### Recruitment and consent

Potentially eligible participants will be identified by clinicians and will be referred to a study investigator who is delegated to provide further information and check eligibility. Eligible participants will be given a Participant Information and Consent Form (PICF) and asked to provide written informed consent prior to commencement in the study. Participants will also consent for the study team to acquire results from other health services for the purpose of the research, to maximise data collection should participants attend for gonorrhoea testing elsewhere during the period of the study. Participants will be able to change or withdraw their consent to participate at any time during the course of the study.

### Interventions

The MenGo trial involves nine study visits over 24 months for each participant, including a baseline visit (month 0) and 3-monthly follow up visits. Table 2 outlines the trial schema. Participants in the ‘4CMenB vaccine arm’ will receive vaccination at baseline (dose 1) and at month 3 (dose 2). Participants who receive the vaccine will have their blood pressure and temperature taken prior to administration of vaccine. All other physical examinations at all time points will be guided by patient symptoms. At baseline and at each 3-monthly follow up visit, participants in both the ‘4CMenB vaccine arm’ and the ‘no treatment arm’ groups will undergo a sexual health screen as per the Australian STI guidelines [28]. Samples taken will include first-void urine for urogenital gonorrhoea and chlamydia by NAAT, oropharyngeal and anorectal swabs for gonorrhoea and chlamydia by NAAT, and blood for HIV, hepatitis and syphilis screening. Urine and swabs for microscopy examination, *Mycoplasma genitalium* testing and other microbiological culture and sensitivity testing may also be collected. Participants with a positive test will be recalled to the clinic for management and treatment as per standard of care. Participants will continue to receive other standard of care testing and treatment as required. A non-standard-of-care blood sample will be collected from both groups at 3, 6, 12 and 24 months post vaccine for analysis of *N. gonorrhoeae-*specific antibodies.

In order to maximise retention in the study, all participants will receive an automated reminder of their next study visit via the clinic electronic reminder system. Participants will routinely be sent an SMS or email reminder of appointments. Participants who failed to attend will be sent two reminders via SMS or email and a final phone call. Unless a participant is discontinued from the study, study visits, procedures and data can continue to be collected at any time from enrolment up to 24 months (+ 14 days). Reasons for discontinuation include participant withdrawal, adverse event, investigator discretion or termination of the study by the Sponsor. Participants who are lost to follow up during the study period will not be replaced.

**Table 2 Tab2:** Study Schema

Month	0 *	3 *	6 *	9*	12 *	15 *	18 *	21 *	24 *	Un-scheduled
Eligibility	√									
Consent	√									
Randomisation	√									
Vaccination	√	√								
Physical examination (BP, temp)	√	√								
Risk Assessment *	√	√	√	√	√	√	√	√	√	√
Sexual health & blood-borne virus test and results *	√	√	√	√	√	√	√	√	√	√
Research blood sample	√	√	√		√				√	
Safety assessment for adverse events	√	√	√	√	√	√	√	√	√	√

*indicates standard of care visits and procedures for participants currently taking PrEP. Study tests and procedures which have been taken within 14 days of the study visit that have already been taken as standard of care for the patient, can be used for study and do not need to be repeated.

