### Study design and setting

MenGO is a Phase III open-label unblinded randomised control trial of 4CMenB vaccination of GBM to protect against *N. gonorrhoeae* infection. The study design is shown in Fig. 1. Participants will be randomly assigned by 1:1 allocation to either: (1) the ‘4CMenB vaccine arm’ who will be vaccinated at baseline and 3 months with 4CMenB; or (2) the unvaccinated ‘no treatment arm’. An STI screen as per the Australian STI guidelines [28] will occur at baseline and at 3 monthly study visits over 2 years. Blood will be collected for antibody analysis at 0, 3, 6, 12, and 24-month visits, and information regarding demographics, concurrent medication, previous gonorrhoea infections, antibiotic use and sexual behaviour risks will be collected at each visit. The trial will be conducted in accordance with the guidelines for Good Clinical Practice (GCP) and will satisfy Consolidated Standards of Reporting Trials (CONSORT) reporting conventions [29].

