### Intervention

Participants will be randomly assigned to either the ‘4CMenB vaccine arm’ or the ‘no treatment arm’ of the study. Participants allocated to the vaccine group will receive a 2-dose schedule of 4CMenB (first dose at baseline visit, second dose at 3-month visit). For each dose, 0.5mL of 4CMenB will be administered by deep intramuscular injection, preferably in the deltoid muscle region of the upper arm. Participants allocated to the no treatment control group will not receive any treatment.

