### Statistical methods

Data analysis will be performed by statisticians at the Gold Coast Hospital and Health Service (GCHHS) who are not involved in other study procedures, to reduce chance of bias in the statistical analysis. The number and percentage of participants with NAAT confirmed *N. gonorrhoeae* from any anatomical site will be presented along with 95% confidence interval (CI) at the completion of the study by treatment group. Total observation time will also be recorded. Associations between 4CMenB vaccination status and the incidence of *N. gonorrhoeae* infection will be investigated using Fisher’s exact test and univariate Poisson regression. The incident rate ratio (IRR) with 95% CIs of incidence of *N. gonorrhoeae* infection in the vaccinated group compared to the unvaccinated group will be calculated. Demographic and clinical characteristics of the 4CMenB vaccinated group and the “no vaccine” group will be compared. If any variables are seen to be different between groups (not expected due to randomization) these will be included in a multivariable Poisson regression model along with 4CMenB vaccine predicting *N. gonorrhoeae* infection. The difference in incidence rates of *N. gonorrhoeae* infections between the study treatment and no treatment at the end of the 2-year study period will also be calculated along with 95% CI. The study treatment will be considered effective if the lower limit of the 2-sided 95% CI for the difference between the incidence rates of gonorrhoea in the study treatment group is 30% lower than the no treatment group. Further analyses may be performed based on the observed differences between the treatments in some subgroups. If it is the case that individual participants record more than one incidence of *N. gonorrhoeae* infection in the period of the study, the same analyses will be performed but using a generalized estimating equations (GEE) approach to Poisson regression to account for within participant correlation.

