Log(base2) transformed antibody, SBA, OPA and neutralisation titres for each of the 0, 3, 6, 12, and 24-month time points will be, initially, compared between vaccinated and non-vaccinated groups by linear regression with log_2_-titre at time 0 as a covariate. Other clinical and demographic covariates will also be tested, along with vaccination status. Variables will be considered as covariates and retained in the model if P < 0.05. Finally, a mixed effects analysis of the trajectory of the log_2_-titres over the 24-month duration of the study will be performed with participant number as a random effect and vaccination status as the fixed effect of interest. Again, other clinical and demographic variables will be tested as covariates.

The number and percentage of treatment-emergent AEs, study treatment-related AEs, SAEs and AEs leading to study withdrawal will be provided.

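### Men discontinued for an adverse event or at investigator discretion stop contributing the primary outcome, and in this open-label trial with an untreated control arm that loss may differ by arm

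*Protocol article*

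**What the plan says.** Two adjacent sentences in the Interventions section of the protocol article (the section with the visit schedule) set the rule. The first is a condition on follow-up: "Unless a participant is discontinued from the study, study visits, procedures and data can continue to be collected at any time from enrolment", up to month 24 with a 14-day allowance. The second lists the grounds: "Reasons for discontinuation include participant withdrawal, adverse event, investigator discretion or termination of the study by the Sponsor". The discontinuation is from the study, not from vaccination. The section adds: "Participants who are lost to follow up during the study period will not be replaced".

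Three other places bear on it.

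- Statistical methods works with the same study-level event in its safety summary: "AEs leading to study withdrawal will be provided".
- Recruitment and consent opens a second source of outcome data: "Participants will also consent for the study team to acquire results from other health services for the purpose of the research". It does not say whether this continues once a man has been discontinued.
- The footnote to Table 2 marks the 3-monthly visits and tests as standard of care for men on PrEP.

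On the design, Study design and setting states: "MenGO is a Phase III open-label unblinded randomised control trial". Intervention states: "Participants allocated to the no treatment control group will not receive any treatment". For the primary outcome, Statistical methods reports the number and percentage of men infected in each arm, then uses Fisher's "exact test and univariate Poisson regression". It also says that total observation time is recorded.

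**The concern.** The intervention is two injections, at months 0 and 3. The outcome is infection over 24 months, found by routine testing. A reason to end a man's participation on safety or discretionary grounds is not in itself a reason to stop recording his NAAT results, yet the two sentences tie one to the other.

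The design makes this matter more than it would under placebo control. A reaction to the vaccine can happen only where vaccine is given, so that route to missing outcome data has no counterpart among controls. Investigators also know the arm when they use discretion. Loss of outcome data may therefore differ by arm for reasons linked to allocation. Loss after a vaccine reaction would tend to come early, when most of the follow-up is still ahead. An analysis plan cannot recover results that were never collected.

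**Working it through.** **What the text does.** Put the two sentences together. Data collection continues unless a man is discontinued from the study; adverse event and investigator discretion are permitted grounds for discontinuation; so for a man discontinued on either ground, collection ends. The consent to obtain outside results does not clearly override this, because the condition in Interventions covers data in general.

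**The plan's own figures.** The article gives no rate of discontinuation for adverse events, so there is no figure to reproduce. The nearest is anticipated attrition of less than 10% from all causes (Sample size), which is fewer than 0.10 × 65 = 6.5 men per arm.

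**Illustration if leavers stay in the denominator.** Inputs:

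- 37.8 cases per 100 person-years (Background and Discussion, for men on PrEP), taken as a constant rate in all participants
- 65 men per arm (Randomisation and allocation)
- a vaccine with no effect
- k vaccinees lost at month 3 and no controls lost on these grounds (assumed)
- lost men counted as uninfected after month 3 (assumed)

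1. Two-year risk: 1 − exp(−0.378 × 2) = 1 − exp(−0.756) = 0.530.
2. Risk by month 3: 1 − exp(−0.378 × 0.25) = 1 − exp(−0.0945) = 0.090.
3. Observed vaccine-arm risk: 0.530 − (k/65) × (0.530 − 0.090).
4. Spurious efficacy: 1 − (observed risk)/0.530.

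| k lost at month 3 | Vaccine arm | Control arm | Spurious efficacy |
|---|---|---|---|
| 1 | 52.4% | 53.0% | about 1% |
| 3 | 51.0% | 53.0% | about 4% |
| 6 | 49.0% | 53.0% | about 8% |

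Timing matters. If the same 3 men left at month 12, risk by then is 1 − exp(−0.378) = 0.315. The shortfall is (3/65) × (0.530 − 0.315) = 0.010, and the spurious efficacy is about 2%.

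**If leavers are dropped from the denominator.** Take the 30% used in Sample size as the true risk in both arms, and suppose the 3 lost men had a risk of 45% to 60% (assumed). The remaining 62 then have a risk of (0.30 × 65 − 3 × 0.45)/62 = 29.3%, or (0.30 × 65 − 3 × 0.60)/62 = 28.5%. Apparent efficacy is 2.4% to 4.8%. If the lost men had average risk there is no bias; if their risk was below average, the sign reverses.

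**Poisson regression.** If recorded observation time enters the model, a man lost at month 3 contributes 0.25 years and his shorter follow-up is accounted for. About 1.75 × 0.378 = 0.66 expected infections per such man go unobserved. The rate ratio is distorted only if leaving is related to infection risk.

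**Scale.** At 53% risk and 65 per arm, the standard error of the risk difference is √(2 × 0.53 × 0.47/65) = 0.088, so the 95% half-width is about 17 percentage points. The 3-man case moves the difference by 2 points, about a quarter of a standard error. Power for 30% against 10% (two-sided, pooled) falls only from 0.821 to 0.799 if 6 vaccinees are lost. The issue is direction of bias, not loss of power.

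**The case against.** The strongest reply is that the text is permissive. It lists reasons that discontinuation may have; it does not say that an adverse event triggers it. A man who reacts to the first dose and does not receive the second can stay in follow-up as the protocol stands. That is right, and a reader who infers that every adverse event removes a man from the trial goes beyond the document.

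Second, a reader might infer that the analysis will count early leavers as uninfected for two years. Statistical methods does not say how they enter the percentage or Fisher's test. That is ordinary content for an analysis plan not shown here, so the point can be made only conditionally.

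Third, only vaccine reactions are confined to one arm. Other adverse events, discretion and withdrawal can occur in both, so a net bias towards the vaccine is possible but not shown.

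Fourth, the losses used above are assumed and all fall early. Six of 65 (9.2%) would take up nearly all the attrition allowed for every cause over 24 months, and Background describes a licensed vaccine with well-documented safety. This stands too, and is why the figures are illustrations.

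Fifth, a full protocol may separate stopping vaccination from ending follow-up, and a condensed article need not. This carries less weight: the article is not silent, but states a condition on data collection and the grounds that end it. The line on adverse events leading to withdrawal is, by itself, a routine safety-table entry and only shows the same study-level wording.

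**Conclusion.** The point holds as a weakness in a stated rule. Men discontinued for an adverse event or by investigator decision stop contributing the primary outcome. Because controls are untreated and the arm is known, that loss may differ by arm.

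If leavers stay in the denominator, the percentage infected and Fisher's test would lean towards the vaccine, since neither adjusts for follow-up time. Poisson regression on observation time would deal with shorter follow-up but not with informative loss.

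The size is unknown and probably small: about 4% spurious efficacy for 3 of 65 vaccinees lost at month 3, within a range of about 1% to 8% for 1 to 6 men. These figures rest on a constant 37.8 per 100 person-years, no vaccine effect, no matching loss among controls, and lost men counted as uninfected. They should not be read as an estimate of bias in this trial. The documents do not support the stronger conclusion that the plan will overstate efficacy. The change is worth making because it is cheap and protects the primary outcome.

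**What to change.** Reconcile Interventions, Recruitment and consent, and Statistical methods so that discontinuation for an adverse event or by investigator decision does not by itself end collection of NAAT results. Scheduled, standard-of-care and outside results would then be collected to month 24, with the man analysed in his randomised arm, unless he withdraws consent to data collection or the study is terminated. State that the consent to obtain outside results continues after such a discontinuation. In the safety summary, make clear whether withdrawal means the end of outcome collection.

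This concerns retention of outcome data only. Whether a man receives a further dose remains a clinical decision, and no rule for it is proposed.

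The cost is mainly wording, since consent to outside results is already sought and the 3-monthly tests are standard of care for men on PrEP. The downside is some extra follow-up effort. It falls mostly on men enrolled because of recent gonorrhoea who are not on PrEP, as the Table 2 footnote does not mark their 3-monthly testing as standard of care.

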### Randomisation and allocation

Participants will be randomized 1:1 to 2 groups of 65 – the ‘4CMenB vaccine arm’ or the ‘No vaccine arm’. A biostatistician independent of the clinical researchers will use the ralloc package of Stata 17 (College Station, Tx., USA) to perform block randomization with blocks of size 2–6. Allocations will be placed in sequentially numbered sealed envelopes and kept in a locked cupboard with restricted access to the area (security pass protected). Randomised allocation will only be performed once written informed consent has been obtained. Investigators will allocate study participants from the sequential sealed envelopes, ensuring that there is blinding of the randomisation process.

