#### Inclusion criteria

GBM who are:

i.Between 18 and 50 years of age.ii.Able to understand spoken and written English.iii.Men who have sex with other men.iv.Able to participate in study procedures including attending for all study visits.v.At risk of acquisition of gonorrhoea at the time of enrolment into the study.vi.Agree to be contacted via phone/ email by the study team.

AND are:

Currently taking HIV pre-exposure prophylaxis (PrEP) at the time of enrolment ORHave been diagnosed with gonorrhoea in the last 3 months.

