## Discussion

A vaccine to protect against *N. gonorrhoeae* infection is urgently needed due to the rising gonorrhoea case numbers and the continued emergence of antibiotic resistance. Despite more than a century of research, only four gonococcal vaccine candidates have been tested in human clinical trials and none of these elicited protection against gonorrhoea [14]. Failures of these early vaccine candidates created hesitancy in the field and delayed gonococcal vaccine development. However, the field has been reinvigorated by recent epidemiological [17, 19, 20, 36–39] and in vitro data [40] suggesting that meningococcal B vaccines may provide cross protection against gonorrhoea.

MenGO is one of the first randomised control trials worldwide that aims to determine the efficacy of the licenced meningococcal B vaccine 4CMenB against gonorrhoea. The trial includes GBM on PrEP, or GBM with a recent *N. gonorrhoeae* infection. This study is limited to GBM due to the high gonorrhoea incidence in this cohort. In Australia, the majority of *N. gonorrhoeae* infections are in GBM [3], and GBM on PrEP have a gonorrhoea incidence of 37.8 cases per 100-person years [5]. Current guidelines for participants taking PrEP recommend 3-monthly review by a health practitioner for testing for STIs [41]. Therefore, participants are unlikely to bear an excess burden to participate in this study. Recent, prior infection with *N. gonorrhoeae* is a risk factor associated with STI diagnosis [42] and is therefore added as an inclusion criterion.

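### Recent gonorrhoea is an entry criterion and a stated risk factor, yet it is neither stratified on nor a fixed covariate, which adds a modest, avoidable variance to the efficacy estimates

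*Protocol article*

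**What the plan says.** **Allocation.** Under Randomisation and allocation: "Participants will be randomized 1:1 to 2 groups of 65", with an independent biostatistician using Stata's ralloc "to perform block randomization with blocks of size 2–6". Allocations go into sequentially numbered sealed envelopes. No stratification factor is named, and the natural reading is one series of envelopes.

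**Entry.** Under Inclusion criteria, a man qualifies by one of two criteria joined by OR: "Currently taking HIV pre-exposure prophylaxis (PrEP) at the time of enrolment", or a gonorrhoea diagnosis in the preceding 3 months. He may meet both. The Discussion explains the second criterion: recent infection "is a risk factor associated with STI diagnosis [42] and is therefore added as an inclusion criterion".

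**Analysis.** Under Statistical methods, the association between vaccination and infection is examined "using Fisher’s exact test and univariate Poisson regression". A rate difference with its 95% CI is also calculated, and the criterion for calling the vaccine effective rests on that interval. Adjustment is conditional: "If any variables are seen to be different between groups (not expected due to randomization) these will be included in a multivariable Poisson regression" model together with vaccination. If men have repeat infections, the same analyses are rerun "using a generalized estimating equations (GEE) approach to Poisson regression to account for within participant correlation". No covariate is fixed in advance for the efficacy analyses, and no adjustment is described for the rate difference.

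**The concern.** Blocking on one list keeps the arm sizes equal over time. It does not balance the arms on a baseline factor. Here the protocol itself identifies a prognostic factor, known at the eligibility check before any envelope is opened, and uses it neither in allocation nor as a fixed model term.

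Fisher's test, the univariate Poisson rate ratio and the rate difference all take whatever imbalance chance produces. The multivariable model is a partial safeguard. It is used only after an imbalance has been noticed, with no stated threshold for calling a variable different, and it is not said to extend to the rate difference. What is at stake is precision, and some freedom over which rate ratio is put forward in an open-label trial. Validity is not at stake.

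**Working it through.** The plan gives no figure of its own on this point, so there is none to reproduce.

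**Inputs from the protocol article.** 65 men per arm, 130 in total (Randomisation and allocation); 37.8 cases per 100 person-years among men on PrEP (Background, Discussion); 2 years of follow-up; 30% vaccine efficacy, so an IRR of 0.70 (Sample size).

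**Assumptions, not in the document.** Share q of men with gonorrhoea in the last 3 months: 20-50%. Rate ratio r for those men against the rest: 1.5-3.

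**Step 1: how often the arms differ.** With K = 130q such men, the number falling in one arm is hypergeometric (130, K, 65). The probability of a gap of 10 points or more is:

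| q | K | P(gap ≥ 10 points) |
|---|---|---|
| 0.2 | 26 | 12% |
| 0.3 | 39 | 25% |
| 0.5 | 65 | 29% |

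The jump from 12% to 25% is partly discreteness: with K = 26 the first gap above 10 points is 8/65 = 12.3, and with K = 39 it is 7/65 = 10.8. A simulation with permuted blocks of 2, 4 and 6 gives 15-26% over the same shares, and about 0% when allocation is stratified.

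**Step 2: what a gap does to the crude IRR.** A 10-point gap multiplies it by [1 + (r−1)(q−0.05)] / [1 + (r−1)(q+0.05)]. For q = 0.3 and r = 2 this is 1.25/1.35 = 0.926. Over q = 0.2-0.5 the multiplier is about 0.96 (r = 1.5), 0.92-0.94 (r = 2) and 0.87-0.91 (r = 3), or the inverse if the gap runs the other way.

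**Step 3: the spread over randomisations.** The SD of the gap is √[2q(1−q)/65], which is 0.0804 at q = 0.3. The SD it induces in log IRR is about (r−1) × SD / [1 + (r−1)q].

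- r = 2: 0.0804/1.3 = 0.0618. The 95% range of the multiplier is exp(±1.96 × 0.0618) = 0.89 to 1.13.
- r = 3: 2 × 0.0804/1.6 = 0.1005. The range is 0.82 to 1.22.

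For scale, 30% efficacy is −ln 0.70 = 0.357 on the log scale. Then ln 1.13 = 0.122 is 34% of it, and ln 1.22 = 0.199 is 56%.

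**Step 4: variance saved.** A simulation used 0.378 per person-year, 2 years, IRR 0.70 and gamma variation between men (shape 1, also assumed). At q = 0.3 the SD of the unadjusted log IRR was:

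- r = 2: 0.303 unstratified, 0.293 stratified. Saving 1 − (0.293/0.303)² = 6.5%.
- r = 3: 0.325 and 0.308. Saving 1 − (0.308/0.325)² = 10%.
- r = 1.5, over the range of q: saving 1-3%.

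The gain depends on the gamma term. With no other variation between men and no vaccine effect, 130 × 0.378 × 2 = 98.3 events give a Poisson variance of about 4/98.3 = 0.0407. At r = 3 imbalance adds 0.1005² = 0.0101, or 0.0101/0.0508 = 20% of the total. That is an upper bound under a homogeneity that is unlikely for repeat infections.

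**Step 5: does adjustment do the same job?** In Poisson simulations without the gamma term (shares 10-50%, r = 1.5-3, no effect), the SD of log IRR was 0.204-0.232 unstratified and unadjusted, 0.202-0.206 stratified, and 0.204-0.208 unstratified but always adjusted. Adjustment alone recovers nearly all of the gain.

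**Step 6: bias and error rate.** In those runs the geometric-mean crude IRR was 0.999-1.002. Type I error with robust (GEE-type) variance was 4.9-5.6%. With plain Poisson variance it was 4.7-5.9% at r = 1.5-2 and 6.8-8.0% at r = 3.

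**The case against.** The case for leaving the plan alone is substantial. Unstratified blocked randomisation of 130 men at one clinic is an accepted design. The plan has an adjusted model, and previous infections are recorded, so a visible imbalance could be handled. Sampling noise dwarfs the imbalance: with the SDs above for r = 2 and a true IRR of 0.70, 95% of estimates fall in 0.70 × exp(±1.96 × 0.303) = 0.39 to 1.27 unstratified, and 0.39 to 1.24 stratified. Power at that IRR hardly moves (about 32-36% against 30-38% in the simulations without the gamma term). Men on PrEP are themselves at high risk, so the contrast within the trial could be small. All of this stands, and it is why the point is minor.

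A reader might infer more than the document supports:

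- **That the efficacy estimate is biased.** Chance imbalance adds variance. A given trial's estimate is shifted conditionally on its imbalance, but there is no systematic error (step 6).
- **That imbalance goes uncorrected.** The multivariable Poisson model could correct for it. The weakness is the trigger and its missing threshold.
- **That the shift rivals the effect sought.** The 95% extreme is about one third (r = 2) to 56% (r = 3) of the log effect.
- **That attendance will differ by entry criterion.** The Table 2 footnote "indicates standard of care visits and procedures for participants currently taking PrEP" suggests why it might, but the same 3-monthly screens and reminders apply to all. Since a man can meet both criteria, a yes/no term for recent gonorrhoea would not separate PrEP users from the rest anyway.
- **That stratification has been ruled out.** The article is silent, and the full protocol is not shown.

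What survives is the adjustment rule. A factor the protocol already regards as prognostic should not enter the model only when the arms happen to look different.

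**Conclusion.** The point holds as a minor improvement. Recent gonorrhoea is an entry criterion, a declared risk factor and known before allocation, but it is not used in the described allocation and enters the efficacy model only if an imbalance is seen. The cost is avoidable variance in the crude IRR and in the rate difference that decides success: about 1-10% of the variance of the log IRR for r = 1.5-3 with gamma variation between men, and up to about 20% only at r = 3 with no such variation. The percentages were worked for the log IRR; the crude rate difference is exposed to the same imbalance. The share of men and the rate ratio are assumptions throughout, and a rate ratio near 1 would leave almost nothing to gain.

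**What to change.** **Main change, Statistical methods.** State that the primary Poisson or GEE model includes vaccination and gonorrhoea diagnosed in the 3 months before enrolment (yes/no), whether or not the arms differ on it. State that the rate difference and its CI are adjusted for the same factor, for example by Mantel-Haenszel weighting over the two strata or by standardisation from the model with robust variance. Keep Fisher's exact test and the univariate IRR as unadjusted supporting results. Fix this before outcomes are examined by arm.

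The cost is one model term and a sentence or two of text. The factor is established at eligibility, so there are no extra men, visits or data. With a log link and a vaccine rate ratio common to both strata, the adjusted and crude IRR estimate the same quantity, so the interpretation does not change.

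**Optional, Randomisation and allocation.** The article says data collection is incomplete but not whether enrolment is open. If it is, the remaining allocation can be stratified by the same yes/no factor, with two ralloc lists and two envelope series. The cost is slightly more envelope handling and possibly one incomplete block per stratum, and the date of the change should be recorded. Because fixed adjustment already recovers nearly all of the gain, nothing important is lost if it is too late. If the full protocol already stratifies, the article needs only a clarifying line and the model should carry that term.
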